### Concealment mechanism {16b}

Since this trial will not be blinded, there are no concealment mechanisms. We use a simple algorithm to randomly pick A (closed reduction) or B (no closed reduction) six times and allocate treatment by order of hospital recruitment.

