### Who will take informed consent? {26a}

Informed consent will be obtained by the attending physician at the emergency department. All physicians will be either trained in the protocol or supervised by someone who is.

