### Sample size {14}

The sample size calculation is based on our primary outcome parameter: the VAS score for pain reported on a daily basis from the visit to the ED until the day of surgery. To find out if the pre-operative pain scores of patients that are refrained from CR are comparable with the scores of the CR group, we will use a non-inferiority test. This requires a non-inferiority margin, which is the biggest difference between the two groups in favor of the CR group, without a statistical difference [28]. The European Medicines Agency advices to base the non-inferiority margin on a difference that is not clinically important [29]. Therefore, our non-inferiority margin is 50% of the minimal clinical important difference (MCID) of the VAS [28]. Based on a systematic review concerning the MCID of VAS scores, a MCID is a context-specific and methodological dependent value [30]. To the best of our knowledge, the MCID of the VAS score for DRFs is unknown. Therefore, we used the MCID of a study that included trauma patients with isolated acute extremity pain [31]. For the description of the MCID of the VAS score, the VAS scale is seen as a 100 mm line. With an MCID of 19.3 mm, our non-inferiority margin will be 9.7 mm (= 50%). As only Bird et al. provide a standard deviation (SD) around the MCID, we will use that value of 15 mm for our sample size calculation [24]. To correct for a cluster-effect we use an intra-cluster correlation (ICC) coefficient between the different hospitals of 0.06, which is generally reported in the literature for hospital processes. To calculate the required sample size, two simulations were run both assuming a fixed number of six clusters (hospitals). In the first simulation, an equal number of subjects per hospital was assumed. Hospitals were randomized to start with treatment A (3 centers) or B (3 centers) in a 1:1 fashion and crossed over after half of the patients were included. For total sample sizes varying from 12 to 502 with increments of 12, 5000 simulations were run for each sample size considered. In each simulation, random data was generated under the specifications described above. A linear mixed model was fitted with a random intercept for cluster and treatment group as fixed effect. A 95% confidence interval was calculated based on the t-distribution with degrees of freedom estimated by the Satterthwaite method. The power was calculated as the percentage of simulations in which the upper limit of the 95% confidence interval was smaller than the non-inferiority margin. From the first simulation, it followed that, using a two-sided alpha of 5%, *n* = 80 patients total would be required in total to demonstrate non-inferiority with a power of 80% (Fig. 1).

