
**Fig. 1 Fig1:**
[figure not shown]
Power curve for simulation 1 assuming of balanced clusters (equal number of patients included per center)

However, in practice, unequal number of patients is expected to be included by each center. Also, seasonal effects should be accounted for in the analysis. Therefore, a second simulation was conducted in a similar way. The number of patients included per center was (roughly) based on the number of eligible patients in the past year (known for 4 hospitals) divided by 2 (assuming that 50% of eligible patients would participate). Inclusion rates for the two hospitals for which this was not known were set equal to the hospital with lowest inclusion rate, resulting in monthly inclusions of 13, 7, 7, 1, 1, 1. Seasonal effects were included by a monthly effect, which were assumed to follow a sine function with a period of 12 months. The SD of the seasonal effects over a 12-month period was set equal to the between cluster SD. The half period (*x* = *π*) was set equal to the moment of cross-over. For sample sizes varying from 60 (two months of inclusion) to 360 (12 months of inclusion), again 5000 simulations were run for each sample size considered. Linear mixed models were fitted including center as random effect and month and treatment as fixed effects. Using a two-sided alpha of 5%, *n* = 120 patients total (rounded to above) would be required in total to demonstrate non-inferiority with a power of 80% (Fig. 2). Accounting for a 10% loss to follow-up, a total of *n* = 134 patients will be included. It should be noted that in the simulations, it was assumed that only one VAS pain will be collected for each patient, while in reality multiple VAS scores (one per day) will be obtained during the period between the visit to the emergency department and the operation. An average VAS pain for each patient will be estimated by a multilevel linear mixed model using random intercept for patient nested within center. Including this aspect in the simulation studies was deemed too complicated, since no reliable estimates for the correlation between daily VAS pain scores in this setting are available. However, following the reasoning that multiple measures will lead to a more precise estimate than a single measure, it can be expected that in practice a higher power will be achieved compared to the simulations and including this is not strictly necessary (i.e., the simulations can be regarded as conservative in this respect).

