### Implementation {16c}

The primary investigator generated the allocation sequence. Patients are enrolled by attending physicians in all participating hospitals. With the cluster randomization, every hospital will know beforehand what intervention to assign.

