## Statistical methods

### Statistical methods for primary and secondary outcomes {20a}

Data for the primary outcome measure will be reported descriptively. Descriptive analysis will be performed in order to report outcome measures for the total population. Continuous data will be analyzed using an independent *t*-test or Mann–Whitney *U* test if not normally distributed. For continuous data, the mean and SD (parametric data) or the median and percentiles (non-parametric data) will be reported. For categorical data, numbers and frequencies will be reported. First, data will be reported for the entire study population. A subgroup analysis will be performed, discriminating between CR or withholding from CR. Differences in outcomes will be analyzed using the unpaired *T*-test in case of normally distributed data or the Mann–Whitney test in case of not normally distributed data. Separate analysis will be performed for average VAS score per patient and average VAS score per day to show both the overall average pain preoperatively and the daily trend towards day of surgery. This will show insight to possible effects on the average caused by patients waiting longer for their surgery. Descriptive analysis will be performed in order to report outcome measures for the total population (main analysis) and (if applicable) the subgroups as mentioned above. For continuous data, the mean and SD (parametric data) or the median and percentiles (non-parametric data) will be reported. For categorical data, numbers and frequencies will be reported. Given the expected low sample size, neither univariate nor multivariable analyses will be done. Trends in PRWE scores will be assessed using generalized linear mixed models calculating the marginal mean differences. Differences in complication rates and re-interventions will be analyzed using the chi-square test of Fisher’s exact test.

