## Discussion

The main practical issue we focus on during this trial is the decision of the attending trauma surgeon whether or not the fracture requires surgical fixation. We trust all participating physicians adhere to the national guidelines, but practice shows at least some amount of inter-observer variability, with several cases of initial conservative treatment, with the intention of avoiding surgery. To monitor this, all exclusions that were eligible for inclusion according to the stated criteria will be kept track of, including the reason for exclusion.

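### Lack of blinding is given as the reason for having no allocation concealment; recruiters know the arm, enrolment can differ by arm, and no planned analysis adjusts for pain at presentation

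*Protocol article*

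**What the plan says.** Protocol article, Concealment mechanism {16b}: "Since this trial will not be blinded, there are no concealment mechanisms". Sequence generation {16a} gives all patients at a hospital the same arm until a cross-over triggered by a local count of inclusions. Implementation {16c} adds: "With the cluster randomization, every hospital will know beforehand what intervention to assign".

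On entry to the trial, section {26a} says: "Informed consent will be obtained by the attending physician at the emergency department". Recruitment {15} has the treating physician inform and invite the patient, and {16c} has attending physicians enrol. The Abstract (Methods) makes the attending surgeon's view that surgery is needed part of eligibility. The Discussion calls that decision the main practical issue and concedes that "practice shows at least some amount of inter-observer variability, with several cases of initial conservative treatment".

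Two analyses of the primary outcome are described. Statistical methods {20a} compares the arms by t-test or Mann–Whitney test and says that "neither univariate nor multivariable analyses will be done". Sample size {14} describes mixed models: centre, month and treatment in the second simulation, and a patient-within-centre random intercept for the daily scores. Neither contains a patient-level covariate.

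**The concern.** Blinding and concealment are separate safeguards. Blinding limits what people know after allocation. Concealment keeps the next allocation from those who decide whether a patient enters. That the trial is open explains the absence of the first, not of the second.

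Here the gap has a route to the result. The people who know the arm judge the indication, make the offer and take consent, and patients may decide knowing which treatment the hospital is giving. If the patients enrolled in reduction and no-reduction periods differ in how much pain they would have had anyway, that difference enters the treatment contrast. Randomising the starting order of six hospitals does not balance selection that happens afterwards. In a non-inferiority comparison a bias towards no reduction makes a false claim of non-inferiority more likely; a bias the other way costs power.

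**Working it through.** **1. The plan's own figures.** Inputs from Sample size {14}: margin 9.7 mm (half of 19.3 mm), SD 15 mm, two-sided alpha 5%, power 80%, six hospitals, ICC 0.06, monthly inclusions 13, 7, 7, 1, 1, 1.

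- Without centre structure: n per arm = 2 × (1.960 + 0.842)² × 15² / 9.7² = 37.5, so 38 per arm, 76 in total.
- Equal centres, with centre in the model: SE = 2 × 15/√n on n − 7 degrees of freedom. Power is 80.4% at n = 78 and 81.4% at n = 80. The plan says 80.
- Unequal centres with fixed month effects, averaged over the 20 ways to choose three starting hospitals: power is 75–78% at n = 90 and 87–89% at n = 120. At 30 patients a month, 120 is the first whole month above 80%. The SE at 120 is about 3.0 mm.
- Loss to follow-up: 120/0.90 = 133.3, so 134.

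The stated numbers reproduce. Selection does not change them; it adds bias that the calculation does not contain.

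**2. Is there room for arm-dependent selection?**

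- Arm known before enrolment: yes, at every hospital ({16c}).
- Switch foreseeable: yes, it follows a local inclusion count ({16a}).
- Discretion in eligibility: yes, the surgical indication is said to vary between observers (Discussion).
- Eligible patients not enrolled: 50% in the second simulation, or a 30% rejection rate in the accrual estimate (both {14}).

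Non-participation gives room for selection. It does not show that selection differs by arm.

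**3. How large could the bias be?** The documents give no selection rate and no link between selection and pain, so the inputs below are assumptions. Only the SD of 15 mm, the 19.3 mm and the 9.7 mm margin are the plan's.

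(a) Case mix: bias = difference in mix × difference in mean pain between the two kinds of patient.

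| Mix difference | Pain difference | Bias | Share of 9.7 mm |
|---|---|---|---|
| 5 points | 10 mm | 0.5 mm | 5% |
| 10 points | 19.3 mm | 1.9 mm | 20% |
| 20 points | 19.3 mm | 3.9 mm | 40% |
| 25 points | 19.3 mm | 4.8 mm | 50% |

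(b) A share p with the highest selection score is left out of one arm only, and the score correlates ρ with the outcome: bias = ρ × 15 × φ(z)/(1 − p), with z the normal quantile at 1 − p. For p = 10%, φ(1.282)/0.90 = 0.195; for p = 30%, φ(0.524)/0.70 = 0.497.

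| Left out | ρ = 0.1 | ρ = 0.3 | ρ = 0.5 |
|---|---|---|---|
| 10% | 0.3 mm (3%) | 0.9 mm (9%) | 1.5 mm (15%) |
| 30% | 0.75 mm (8%) | 2.2 mm (23%) | 3.7 mm (38%) |

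**4. What a given bias does** (SE 3.0 mm, normal approximation). With a true difference at the margin, a bias b towards no reduction gives a one-sided error of Φ(b/3.0 − 1.96): 2.5% at b = 0, about 10% at b = 2 mm (21% of the margin), about 37% at b = 4.85 mm (half the margin). With no true difference, a bias b against no reduction gives power Φ((9.7 − b)/3.0 − 1.96): about 90% at b = 0 and 73% at b = 2 mm.

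**The case against.** The strongest defence is that the protocol already narrows the room for selection. Eligibility criteria {10} give mostly numeric radiographic thresholds. The exclusions remove, in both arms, severe presentations that a physician might otherwise hold back from the no-reduction arm: limb-threatening ischaemia, skin tenting or impending open fracture, and acute median nerve symptoms. Section {11b} lets the physician reduce after all for neurovascular symptoms, which weakens a motive not to enrol. The Discussion promises a log, with reasons, of eligible patients who were excluded. Advance knowledge of the arm also follows from allocating by hospital, which {16a} justifies by round-the-clock recruitment, and covariates are often left to an analysis plan.

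Most of this stands as mitigation, but none of it prevents selection. The offer, the consent and the judged indication remain open to knowledge of the arm, and a log shows selection only afterwards. On covariates, {20a} does not leave the matter open: it rules multivariable analysis out.

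Three stronger readings are tempting and are not supported.

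- A reader might infer that the protocol calls concealment impossible. It says only that there is none; the words about impossibility in {17a} concern blinding.
- A reader might infer that non-inferiority is favoured, because severe cases would be kept out of no-reduction periods. The Introduction also describes reduction as painful and possibly traumatising, so refusal in reduction periods is just as conceivable. The sign is unknown.
- A reader might infer that losing the 10% of patients with most pain from one arm costs 30% to 50% of the margin. The arithmetic is right (0.195 × 15 = 2.9 mm, 30%), but it selects on the outcome itself, an average over the days up to surgery, usually 7 to 14, which nobody at the ED can see. The 50% needs an SD of 25 mm (0.195 × 25 = 4.9 mm), which is not in the documents. Weaker links give 3% to 15% for the same 10%.

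**Conclusion.** The structural point holds on the text. The reason given for having no concealment is wrong, recruiters know the arm, the entry decision has admitted discretion, and neither analysis described adjusts for pain at presentation. Enrolment can therefore differ by arm, and the existing safeguards limit or reveal this without preventing it.

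The size is not established. Under the assumptions shown, the bias runs from about 3% of the margin (10% left out, correlation 0.1) to about 50% (a 25-point difference in mix and a 19.3 mm difference in pain). These are illustrations, not bounds, and the bias could favour either arm. A bias of 2 mm towards no reduction would already raise the one-sided error at the margin about fourfold. The sample size itself is not called into question by this point.

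**What to change.** Keep the cluster cross-over design and the sample size, and make these changes:

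1. In {16b}, drop lack of blinding as the reason. State that recruitment is unconcealed because allocation is by hospital and period, and name selection bias as a limitation.
2. Adjust the primary mixed model for age and for the ED VAS, replacing the statement in {20a} that no multivariable analysis will be done. Section {18a} already has a VAS taken before plaster; specify that it is taken before any reduction as well, and keep it out of the outcome average.
3. Before the study is offered, record from the presenting radiograph which criterion of {10} the patient meets.
4. Report the log promised in the Discussion, and the fraction of eligible patients enrolled, by arm and period.

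The cost is slightly more recording at the sites and some analysis work, with no extra visits. Trial status gives recruitment as under way, so item 3 and any change in the timing of the VAS can apply only to patients still to come, while the model and the reporting can be fixed at any time before analysis. The limit should be stated: adjustment removes only the selection that acts through age and recorded baseline pain, and none of these steps creates concealment.

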### Implementation {16c}

The primary investigator generated the allocation sequence. Patients are enrolled by attending physicians in all participating hospitals. With the cluster randomization, every hospital will know beforehand what intervention to assign.

## Assignment of interventions: blinding

### Who will be blinded {17a}

This is an open-label study, and blinding is not possible.

### Procedure for unblinding if needed {17b}

The design is open label, so unblinding will not occur.

## Data collection and management

### Plans for assessment and collection of outcomes {18a}

The primary outcome is the average of the pre-operative visual analog scale for pain (VAS) score, reported on daily basis from the ED visit until operation. The VAS score is an easy, valid, and reliable tool for pain measurement that has been widely used [32]. The VAS score will be presented as a horizontal line with in which the complete left side is defined as “no pain,” and the complete right side is defined as “the most extreme pain possible.” The patients will be asked to mark the position that corresponds with their pain experience. The VAS score prior and after the plaster application will represent their current pain experience. During the ED visit, patients will receive a “pain diary,” containing multiple empty VAS forms. Patients will be asked to report their average VAS score at the end of every day as well as the worst pain of that day (the latter will be used for a secondary analysis). The average will be calculated by adding all pain scores and dividing by the number of days for each patient. Besides the pre-operative VAS scores, they will also register the post-operative VAS score at 6 weeks and at 3, 6, and 12 months. The following parameters will serve as secondary outcome measures.

Average pain per day, average highest pain, and highest pain per day will all be analyzed to identify possible patterns secondary to the primary outcome of average pain from day 1 until surgery. The post-operative Patient-Rated Wrist Evaluation (PRWE) score [33] after 6 weeks and 3, 6, and 12 months will be assessed. The PRWE is a 15-item questionnaire designed to measure wrist pain and disability in activities of daily living. The PRWE allows patients to rate their levels of wrist pain and disability from 0 to 10 and consists of 2 subscales:Pain subscale: contains 5 items each of which is further rated from 1 to 10. The maximum score in this section is 50 and minimum 0Function subscale: contains total 10 items which are further divided into 2 sections, i.e., specific activities (having 6 items) and usual activities (having 4 items). The maximum score in this section is 50 and minimum 0

The length of stay in the ED will be measured in minutes and concerns the entire time that a patient is present in the ED. This will be calculated by subtracting the registration time from the discharge time.

The type and quantity of painkillers used by the patients will be registered. In the ED, the pre-trauma painkiller use will be registered. Furthermore, the patient will be asked to keep records of their painkiller use in the diary on daily basis until operation.

Patient satisfactions with cosmetic result, functional result, and activity resumption will be determined at 12 months using a 10-point numerical rating scale (NRS), in which 0 implies extremely dissatisfied and 0 implies extremely satisfied.

Physical examination of range of motion (ROM) of the wrist will be measured actively with a goniometer in degrees. This will include palmar and dorsal flexion, ulnar and radial deviation, and pronation and supination of the wrist.

Grip strengths will be measured using a dynamometer as the mean of three measurements. Grips strength will be measured in kilograms.

The general quality of life will be measured with the EQ-5D-5L questionnaire. This questionnaire consists of five items, measuring at 5-point scales whether patients experience problems and to what extent, with regard to their mobility, self-care, daily activities, pain, and mood.

All described complications in the patient record will be reported, including, but not limited to, carpal tunnel syndrome (CTS), compartment syndrome, bleeding, infection, malunion, and revision surgery.

At the end of the study, we will assess whether CT scans of DRFs after CR are better to assess in pre-operative planning than CT scans of DRFs that did not have CR. Also, we will test inter-observer variability. Multiple experts will classify the fracture according to the AO classification on X-ray and CT scan. This will be blinded so the expert does not know which X-ray belongs to which CT scan.

The balance between costs and impact of refraining from CR in the ED will be assessed by performing a cost-effectiveness analysis. This will address the question whether or not withholding from CR is saving costs in ED. Cost-effectiveness will be calculated with the EQ-5D-5L, the iPCQ, and the iMCQ.

### Plans to promote participant retention and complete follow-up {18b}

Since participation to this study requires no extra hospital visits, we expect high follow-up percentage. Physical measurements will be taken at standard post op checkups at 6 weeks and 3 months; all other questionnaires will be sent by email or taken over the phone.

### Data management {19}

Data will be collected in Castor EDC. Data will be entered by study personnel from source documents kept in a locked storage. External data monitoring will take place at the start, half way, and at the end of the study.

### Confidentiality {27}

All participants will be given a site-specific number. As stated above, data will be stored in the save digital environment of Castor EDC, and physical forms will be stored in a locked storage. The data will only be accessible for the study personnel and an external monitor. All published data will be anonymized.

